#### Goals and hypotheses

2.2.2.

The main goal of #EntreViagenseAprendizagens is to promote well-being and healthy lifestyles among adolescents. Specifically, the program aims to: (a) foster social and emotional skills (particularly self-regulation, communication, problem-solving, resilience, and adaptability); (b) identify and strengthen the students’ virtues and character strengths, which contribute to the definition of their life purpose and to their ability to adapt; (c) increase general health literacy and mental health literacy; (d) improve knowledge and behaviors related to healthy lifestyles, especially physical activity and healthy eating; and (e) improve overall well-being. Indirectly, the program also serves the purpose of preventing the development of social and emotional adjustment problems (e.g., anxiety, depression, behavioral problems).

We hypothesize that the #EntreViagenseAprendizagens program will result in (1) a significant increase in social and emotional skills (self-control, cooperation, empathy, and stress resistance); (2) a significant decrease in emotion regulation difficulties (specifically, limited access to emotion regulation strategies and lack of emotional clarity); (3) a significant increase in general health literacy and mental health literacy (specifically, self-help strategies, first-aid skills and help-seeking, and knowledge about mental disorders); (4) a significant increase in knowledge about nutrition and physical activity; (5) a significant increase in health-related attitudes and behaviors (e.g., increase in physical activity and healthy eating, decrease in screen time); (6) a significant improvement in the perception of the quality of relationships with others (specifically, peer acceptance and relationships with mother and father); and (7) a significant increase in adolescent well-being (specifically, engagement, perseverance, optimism, connectedness, and happiness). We also hypothesize that the results will be maintained at the 9-month follow-up.

#### Structure of sessions with students

2.2.3.

The sessions are implemented with groups of 12–15 students, with one facilitator per group. All sessions have clearly defined learning goals, and are dynamic and interactive, with a duration of 50 min (i.e., the same duration as regular curricular classes, in order to maximize the adolescents’ attention and encourage adoption of the program by creating the possibility of integrating it into regular curricular units). Most sessions are structured as follows: a semi-structured individual (or group) activity, a semi-structured activity in small groups, and a final interactive debate on what was learned during the session.

Although there are always one or two key skills that are the focus of each session, in the same session several competencies can be worked on, given their association with different themes and the use of different types of activities. For example, in session #14, titled “Parliament,” the main theme is communication (focusing on assertive communication as an important social and emotional skill); however, the themes covered in the scenarios presented to the students for the role-play concern different issues, such as (un)healthy behaviors, making it possible to work on health literacy at the same time.

At the end of each session, a “healthy tip” associated with the topic that was addressed during that session (e.g., #gratitude) is discussed and complemented with a “challenge of the week.” This challenge is an intersession activity to be developed during the week (e.g., “gratitude agenda”) and related to the content of the session. This activity can be shared and discussed at the next session if the participants so wish.

In the first session, each student will receive a folder in which to place all the activity sheets completed during the program. This folder will then serve as a portfolio and a record of the student’s evolution and involvement.

#### Involvement of students’ parents

2.2.4.

Before the program begins, all parents/guardians of students in the intervention group will be invited to attend an online session, where the objectives of the program will be presented and doubts will be clarified. This session aims to promote family involvement from the beginning of the program and to motivate families to participate in some of the challenges of the week. As defined by the American Psychological Association (2023), school-based interventions should include special homework assignments to be completed with parents. Therefore, alerting parents to its relevance is essential from the start.

The fourth session of the program is aimed at the parents/guardians, focusing on their role in promoting the well-being of the students. In this session, the parents will also be asked to vote on a topic they consider relevant to be subsequently included in the “surprise” session of the program (session 17). Examples of such topics are bullying and peer pressure.

#### Photo contest “well-being-promoting actions”

2.2.5.

The program includes a photography competition, titled “Well-being-Promoting Actions,” associated with the photovoice methodology (Wang and Burris, 1997) and run on the program’s Instagram® account. The contest aims to promote the involvement of the students, their families, the school community, and the community in general as well as amplify the effect of the intervention. The use of photovoice will allow students to engage their creativity and become more interested in reflecting and writing about their well-being, increasing their well-being literacy (Oades et al., 2021). It will also contribute to improving their self-esteem and self-determination, as the students feel respected and considered (Golden, 2020).

Students will take a photo of something they do that they think contributes to their well-being and write a five-line paragraph explaining why they chose it and what the photo says about their perception of health and well-being. The photos will be posted on the Instagram^®^ page of #EntreViagenseAprendizagens, where the voting will take place. In each school, the three best photographs (with the most “likes”) will be elected, and their authors will receive a prize (e.g., book/music shop vouchers). The competition may result in a photo exhibition at the schools, at the end of the school year. The aim of the exhibition is to integrate the learnings acquired during the program and showcase them to the rest of the school, thus promoting a sense of belonging and normalization of the themes addressed. This exhibition may also help the whole school community to reflect on these themes.

#### Context of implementation and facilitators

2.2.6.

The program can be implemented in two different formats: (a) integrated into an 8th or 9th grade subject at the choice of each school (e.g., Citizenship and Development), running for two periods of the school year; (b) as an extracurricular activity of the schools. The first option allows for a greater number of participants and a broader scope of the program. In the evaluation study of #EntreViagenseAprendizagens, only students from the 8th grade attending the regular curriculum (subject of Citizenship and Development) will be included.

The program will be facilitated by psychologists with a master’s degree in Psychology, preferably with experience in therapeutic intervention with adolescents. The facilitators will receive training from the first author (project coordinator) regarding the #EntreViagenseAprendizagens program, which will cover, among other aspects, the objectives and contents of each session. Biweekly follow-up meetings with the project coordinator will be held to deal with any unforeseen circumstances that may arise, highlight important aspects of each session, deliver materials, monitor the adequacy and fidelity of the implementation, and brainstorm about aspects that might be improved.

### Intervention impact evaluation

2.3.

#### Design and procedure

2.3.1.

A cluster randomized controlled trial design will be used for impact evaluation, with 8th grade classes (units of randomization) from three public schools being assigned to either the intervention or the control condition. Data collection will be based on structured questionnaires applied to all students, both in the control group and the intervention group. Baseline measures (T0) will be collected with all potential participants prior to intervention implementation. In each school, three classes will then be randomly selected to be part of the intervention group in Year 1, while the remaining classes will be the control group. Students who integrate the control group in Year 1 will be part of the Intervention Group in Year 2. The post-test (T1) will take place approximately 1 week after the end of the program and the follow-up (T2) will take place 9 months later.

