#### Data analysis

2.3.3

Descriptive statistics will be used to describe intervention and control group participants, replying to the pre-test, post-test, and follow-up questionnaires. To assess intervention effectiveness, statistically significant differences (and effect sizes) between the intervention and control groups will be examined by repeated measures ANOVA, contrasting results from the intervention and control groups (between-subjects factor) on the different outcome measures (e.g., social and emotional skills, health literacy, well-being) at pre-test, post-test, and follow-up (within-subjects factor).

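### Classes are randomised within school, three to intervention and the rest to control, but the stated ANOVA has no school term, so school differences can enter the programme contrast if the schools have unequal numbers of classes

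*Protocol article*

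**What the plan says.** Section 2.3.1 (Design and procedure) describes a cluster randomised trial with "8th grade classes (units of randomization) from three public schools being assigned to either the intervention or the control condition". The draw is made school by school: "In each school, three classes will then be randomly selected to be part of the intervention group in Year 1, while the remaining classes" serve as controls. The intervention count is thus fixed at three per school (nine in all). The control count is whatever is left, and the article does not state it.

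Section 2.3.3 (Data analysis) says that differences "between the intervention and control groups will be examined by repeated measures ANOVA". Group is the only factor named on the between-subjects side: "contrasting results from the intervention and control groups (between-subjects factor) on the different outcome measures". Time (pre-test, post-test, follow-up) is the within-subjects factor. School does not appear in the impact analysis as a factor, block or covariate, and the article does not say which ANOVA term is the test of effectiveness.

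**The concern.** Randomisation makes the arms comparable within a school. Across schools they are comparable only if every school has the same ratio of intervention to control students. A fixed three per school does not secure that: the chance of intervention is 3/K, where K is the school's number of 8th grade classes. If K varies, the intervention arm draws equally on the three schools, while the control arm draws more heavily on the school with more classes. A contrast that ignores school then combines the programme effect with differences between schools. This would be an expected bias built into the allocation, not a chance imbalance, and its direction would depend on which school does better.

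**Working it through.** **Inputs from the article:** three schools; three intervention classes in each; all other classes control; group and time as the named factors; three time points. The article gives no class counts, class sizes, intraclass correlation (ICC) or sample size, so there is no stated figure to reproduce. All values of these below are assumptions. *Smallest* and *largest* mean the schools with fewest and most 8th grade classes.

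**Formula.** With equal-sized classes and no programme effect, school s has weight 1/3 in the intervention arm and (K_s − 3)/Σ(K − 3) in the control arm. If μ_s is the school's mean on the quantity analysed,

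bias = Σ [1/3 − (K_s − 3)/Σ(K − 3)] × μ_s.

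**Worked case, 4, 6 and 8 classes.**
- Chance of intervention: 3/4 = 75%, 3/6 = 50%, 3/8 = 37.5%.
- Control classes: 1, 3 and 5, so control weights are 1/9, 3/9 and 5/9, against 3/9 each in the intervention arm.
- Weight differences: +2/9, 0 and −2/9.
- Bias = 2/9 × (μ_smallest − μ_largest). For a 0.3 SD difference this is 0.067 SD; for 0.5 SD it is 0.111 SD.

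**Range over assumed class counts** (middle school halfway between the other two):

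| Classes | Share of the smallest-minus-largest difference | 0.1 SD | 0.3 SD | 0.5 SD |
|---|---|---|---|---|
| 6, 6, 6 | 0 | 0 | 0 | 0 |
| 5, 6, 7 | 1/9 | 0.011 | 0.033 | 0.056 |
| 4, 5, 6 | 1/6 | 0.017 | 0.050 | 0.083 |
| 4, 6, 8 | 2/9 | 0.022 | 0.067 | 0.111 |
| 4, 4, 10 | 1/3 | 0.033 | 0.100 | 0.167 |

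**Class size.** What counts is the ratio of intervention to control students in each school. If counts are equal and all classes within a school have the same size m_s, both arms have weights m_s/Σm and the bias is zero. Class sizes matter where they make that ratio differ between schools.

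**Which ANOVA term.** For the group main effect, μ_s is the school's level averaged over time. For group-by-time, μ_s is the school's change, because a stable difference in level subtracts out.

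**Simulation check.** 4,000 trials per case, 22 students per class, pre and post only, baseline and change SD each set to 1, no programme effect, two-sided 5% tests:

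| Case | Term tested | Bias (SD) | Type I error | With school as fixed effect |
|---|---|---|---|---|
| 6, 6, 6; schools differ by 0.4 in level and change; class ICC 0 | group-by-time | 0.00 | 5.1% | 0.00; 5.3% |
| 4, 6, 8; 0.4 in level only; ICC 0 | group-by-time | 0.00 | 5.3% | 0.00; 5.2% |
| Same | main effect | 0.09 | 11.9% | not run |
| 4, 6, 8; 0.2 in change; ICC 0 | group-by-time | 0.04 | 7.4% | 0.00; 5.1% |
| 4, 6, 8; 0.4 in change; ICC 0 | group-by-time | 0.09 | 14.2% | 0.00; 5.2% |
| 4, 6, 8; 0.4 in change; ICC 0.05 | group-by-time | 0.09 | 24.3% | 0.00; about 17% |

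The last row shows that the school term removes the bias but not the excess false positives that come from ignoring class.

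**Cost of omission when counts are equal.** School means of +0.2, 0 and −0.2 SD have variance (0.04 + 0 + 0.04)/3 = 0.027. Leaving school out therefore adds about 2.7% to a within-school variance of 1. That is a small loss of precision and does not raise the false-positive rate.

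**The case against.** The strongest reply has three parts.

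1. **The bias depends on facts that the article does not give.** It needs unequal arm ratios across schools, and the schools may have the same number of classes. This stands: the bias is conditional. The design as written does not guarantee equality, however.

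2. **The natural test is group-by-time.** The hypotheses in section 2.2.2 are about increases and decreases, and stable school differences in level cancel in that term. This stands too. A 0.067 SD bias in group-by-time needs schools to differ by 0.3 SD in how much students change, which is a stronger assumption than a 0.3 SD difference in level. Since section 2.3.3 does not name the term, the main effect cannot be ruled out as the test.

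3. **Stratification terms can be left to an analysis plan that is not shown.** Such a plan could add school. But the article names the model and its factors, and that model does not match the allocation described two sections before. The point rests on what is stated.

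A reader might also go further and infer that control students come mostly from the largest school, or that the bias vanishes only when class counts are equal. Neither follows. With 4, 5 and 6 classes the largest school supplies 3 of 6 control classes, exactly half. With 4, 6 and 8 classes the bias is zero whenever the smallest and largest schools have the same mean, whatever the middle one does.

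**Conclusion.** The mismatch is established: school is a stratum of the randomisation and is absent from the stated effectiveness model. Its consequence is conditional. If the arm ratio differs between schools, school differences in level bias the group main effect and school differences in change bias group-by-time. In the assumed cases the bias runs from zero to 1/3 of the difference between the smallest and largest school, with 2/9 in the 4, 6, 8 illustration. That is small to moderate, and it can go in either direction. With equal counts and class sizes there is no bias and the loss is mainly in precision.

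The article does not support saying that the programme effect will be biased, or by how much. Nor would a school term alone make the analysis sound, because class, the unit of randomisation, is a separate matter in the same model. The change is worth making because it is cheap and protects the contrast whatever the class counts prove to be.

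**What to change.** Add school and school-by-time as fixed effects to the effectiveness model, so that the programme effect is the within-school contrast pooled over the three schools. Do this in a model that also accounts for class as the unit of randomisation, and name the term that tests effectiveness. Report the number of classes, and preferably students, per arm in each school, so that readers can see how far the ratios differ.

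The cost is a few degrees of freedom: 3 − 1 = 2 for school and (3 − 1) × (3 − 1) = 4 for school-by-time over three time points. No new data are needed, since each student's school is already known.

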**Methods:**

This protocol describes a school-based intervention, #EntreViagenseAprendizagens, that will be implemented in several schools in Portugal. The program is aimed at 8th and 9th grade students (14–16 years old) and comprises 20 weekly sessions. One of the sessions is aimed at the students’ parents/guardians. The intervention content targets social and emotional skills, health literacy (physical and mental health), healthy lifestyles, character strengths, and well-being. An experimental design will be used in the intervention evaluation. Eighth grade classes will be randomly assigned to the intervention group or the control group. All students complete the same assessment protocol at baseline, post-intervention, and 9-month follow-up. The impact assessment protocol includes measures related to well-being, health literacy, health-related knowledge, attitudes and behaviors, relationships with others, social and emotional skills, and sociodemographic data. Process evaluation includes evaluation forms at the end of each session and at the end of the program and focus groups with students, parents, and teachers at the end of the program.

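### The 9-month follow-up falls in the year when controls receive the programme, and nothing makes control delivery wait for it, so the planned T2 contrast may not be able to test maintenance

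*Protocol article*

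**What the plan says.** Section 2.3.1 (Design and procedure) sets up a class-randomised trial: "A cluster randomized controlled trial design will be used for impact evaluation, with 8th grade classes (units of randomization) from three public schools". Allocation follows baseline and is made separately by site, under this rule: "three classes will then be randomly selected to be part of the intervention group in Year 1, while the remaining classes will be the control" arm. Those controls are then scheduled to cross over: "Students who integrate the control group in Year 1 will be part of the Intervention Group in Year 2".

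The timing is fixed in two places. The Abstract says that the programme "comprises 20 weekly sessions". Section 2.3.1 puts the post-test (T1) about one week after the programme ends, and "the follow-up (T2) will take place 9 months later". Section 2.2.6 adds that the curricular format has the programme "running for two periods of the school year". The Abstract also says that all students, in both arms, complete the assessment at all three waves.

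Section 2.3.3 (Data analysis) names one effectiveness analysis, a repeated measures ANOVA with intervention versus control as the between-subjects factor, "at pre-test, post-test, and follow-up (within-subjects factor"). Section 2.2.2 states the hypothesis that depends on the last wave: "We also hypothesize that the results will be maintained at the 9-month follow-up".

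The article gives no calendar dates for Year 1 or Year 2, no rule on the order of T2 and control delivery, and no separate treatment of T2 for controls who have crossed over.

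**The concern.** In a waiting-list design the randomised comparison is between treated and untreated only until the waiting group starts. Here the follow-up wave falls in the year when the waiting group starts, yet the analysis keeps calling those students controls.

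If they have begun the programme by T2, the contrast is no longer between programme and no programme. It compares students who finished nine months ago with students who are part-way through or done. A narrower difference at T2 could mean that the effect faded or that the controls caught up, and the planned ANOVA cannot tell these apart. If the programme works, the bias runs towards missing maintenance, not towards claiming it falsely. The hypothesis at stake is the maintenance hypothesis; the seven numbered hypotheses in section 2.2.2 can still be tested at T1.

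**Working it through.** The article states no sample size, power or effect size, so there is no figure of its own to reproduce. The check is a timeline, followed by an illustration of size.

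**Inputs from the article.** 20 weekly sessions (Abstract); T1 about 1 week after the end and T2 9 months after T1 (section 2.3.1); control delivery in Year 2 (section 2.3.1).

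**Assumptions.** Years 1 and 2 are consecutive school years; a year has 52.18 weeks, so 9 months = 9 × 52.18 / 12 = 39.1 weeks; the school year lasts 39 weeks.

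**1. When T2 falls, counted from the first Year 1 session.**
- No school breaks: 20 + 1 + 39.1 = 60.1 weeks (13.8 months), which is 60.1 − 52.2 = 8 weeks past the anniversary of the start.
- With 2, 4 or 6 break weeks during the programme: 62.1, 64.1 or 66.1 weeks, which is 10, 12 or 14 weeks past the anniversary.

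**2. Whether T2 can fall outside Year 2.** Count weeks from the start of the Year 1 school year.
- The earliest possible programme end is week 20, so T2 is no earlier than 20 + 1 + 39.1 = week 60.1, after Year 2 opens at week 52.2.
- If the programme ends within the school year (week 39), T2 is no later than 39 + 1 + 39.1 = week 79.1, before Year 2 closes at 52.2 + 39 = week 91.2.
- T2 therefore lies in Year 2 for any start date, between about week 8 and week 27 of that school year.

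**3. Control exposure at T2.**
- Year 2 on the same calendar as Year 1: about 8 of 20 sessions (8/20 = 40%) with no breaks, and at most about 12 with 4 break weeks.
- Year 2 delivery held until after T2: 0 sessions.
- Late Year 1 start but early Year 2 start: T2 can come after week 20 of Year 2, so all 20 sessions are possible.

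**4. Whether holding delivery until after T2 leaves room for 20 weekly sessions.** Weeks left in Year 2 = 91.2 − T2 (week of the Year 1 school year), for 0 to 4 break weeks in Year 1:

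| Year 1 start (school week) | Weeks left after T2 |
|---|---|
| 0 | 27–31 |
| 4 | 23–27 |
| 8 | 19–23 |
| 13 | 14–18 |

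An early start leaves room, week 8 is marginal, and week 13 or later does not. Breaks in Year 2 after T2 would tighten this further.

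**5. Illustration of size.** Every input here is assumed: 200 per arm, standardised effect d = 0.25, correlation 0.6 between waves, no clustering, two-sided 5% test, benefit proportional to sessions.
- Apparent T2 difference when the effect is fully maintained: 0.25 × (1 − 0.40) = 0.15.
- Standard error of a difference in change: √(2 × (1 − 0.6)) × √(2/200) = 0.0894.
- T0-to-T1: 0.25 / 0.0894 = 2.80, power 80%, whatever happens at T2.
- T0-to-T2: power 80% if controls are unexposed; 0.15 / 0.0894 = 1.68, power 39%, if they have had 40% of the programme.
- Three-wave group-by-time test, noncentrality = (200/2) × Σ(dₜ − mean)² / (1 − 0.6). For differences (0, 0.25, 0.25) this is 100 × 0.04167 / 0.4 = 10.4, power 83%. For (0, 0.25, 0.15) it is 100 × 0.03167 / 0.4 = 7.9, power 71%.

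Classes are the randomised units, so real power would be lower throughout.

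**The case against.** The strongest reply is that being in Year 2 is not the same as being exposed. Section 2.3.1 gives no start date for control delivery, the programme occupies only two periods of a school year, and with an early Year 1 start all 20 sessions would fit after T2. An unexposed control group at T2 is compatible with every sentence in the article. A condensed article may also leave a delivery calendar to the full protocol.

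Much of this stands. A reader might infer that the T2 comparison is certainly contaminated; the article does not support that, because exposure could be nil. But this is more than a missing detail. The article itself fixes the crossover year, the T2 interval, who is assessed at T2, the contrast at T2 and the hypothesis resting on it. These fit together only under a sequencing rule that it does not state, and that is workable only for some start dates.

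A reader might also infer that the main result is compromised. It is not: T0 and T1 are both collected before any crossover. Only a test pooling all three waves would be diluted, and section 2.3.3 does not say that a single pooled interaction decides effectiveness.

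Finally, the power figures rest on inputs that the article does not give. They show direction and possible scale and do not measure this trial.

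**Conclusion.** The point holds conditionally. By the article's own intervals T2 lies in Year 2, the year in which controls are moved into the intervention, while the analysis still treats them as controls and the maintenance hypothesis depends on that wave. Unless control delivery is sequenced after T2, controls will be partly or wholly exposed, and the T2 contrast could not test maintenance.

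Exposure is about 8 of 20 sessions on a repeated calendar with no breaks, within a range of 0 to 20 because the Year 2 start is not given. That T2 falls in Year 2 rests only on consecutive school years and a programme that ends within its school year. The size of any distortion rests on assumed inputs and is essentially unknown.

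**What to change.** Sections 2.3.1, 2.3.3 and 2.2.2 must be reconciled.

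1. Estimate effectiveness as the randomised T0-to-T1 contrast, separately from T2.
2. Make a between-group claim at T2 only if T2 is complete in every class before any control student's first session. There are two ways to meet this condition, and the choice is the investigators':
   - Control delivery begins after T2. This keeps the 9-month interval, but 20 weekly sessions then fit only if Year 1 starts early.
   - T2 is measured before control delivery begins. On a repeated calendar that means by about week 52, so the follow-up is 52.2 − 21 = 31 weeks (7.2 months) with no breaks, or 27 weeks (about 6.3 months) with 4 break weeks. The 9-month hypothesis would need rewording.

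   If neither is feasible, report T2 as uncontrolled follow-up of the intervention arm, with no controlled maintenance claim.
3. Record how many sessions each control student attended before T2.

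The edits are a timing sentence and some analysis wording. The real cost is one of three things: a later Year 2 start, a follow-up about 2 to 3 months shorter, or loss of the controlled maintenance claim. The order of T2 and control delivery cannot be repaired once delivery has begun.
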